#### Secondary outcomes

The secondary outcomes include HBV DNA negative rate, HBsAg negative rate, HBeAg seroconversion rate, liver function (ALT, aspartate aminotransferase [AST], gamma-glutamyl transferase [GGT], alkaline phosphatase [ALP], serum albumin [ALB], and total bilirubin [TBIL]), spleen thickness, and the evaluation scores of patients’ clinical symptoms.

These indicators are observed before the treatment, at 26 weeks of treatment, at 52 weeks of treatment, at the 26 ± 2 weeks follow-up period, and at the 52 ± 2 weeks follow-up period.

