## Background

Chronic hepatitis B (CHB) is a chronic viral infection caused by hepatitis B virus (HBV) and characterized by the persistence of hepatitis B surface antigen (HBsAg) for at least 6 months (with or without concurrent hepatitis B e antigen [HBeAg]). As a global health problem, more than 257 million people worldwide suffer from chronic HBV infection [1, 2]. In 2015, an estimated 887,000 deaths resulted from hepatitis B, mostly from cirrhosis and hepatocellular carcinoma (HCC, i.e., primary liver cancer) [3]; of these CHB is responsible for 30% of all deaths from cirrhosis and 40% of those from HCC [4–6]. China’s prevalence is one of the highest, with about 20 million CHB cases, accounting for 21.5% of the 93 million cases of HBV infection. Without timely testing and treatment, most CHB will develop into cirrhosis, HCC, or finally lead to death [7, 8]. It is estimated that in China there are 20–30 million people with CHB, 1 million with liver cirrhosis, and 0.3 million with HCC caused by hepatitis B [9]. Deaths due to HBV-related liver diseases in China (0.308 million deaths per year) account for more than 30% of the global mortality from HBV (0.887 million deaths per year) [10]. Antiviral therapy is the primary link to slow the conversion of CHB into cirrhosis and can effectively restore liver function and improve survival rate in patients with CHB [11, 12]. Currently, the US Food and Drug Administration (FDA) has approved two types of anti-HBV drugs: interferon (IFN) and nucleos(t)ide analogs (NAs, e.g., entecavir, lamivudine, telbivudine, adefovir, and tenofovir). Although NAs are well tolerated and exhibit an early and potent antiviral effect, the selection of resistant mutants and nephrotoxicity during long-term therapy limit their use [13, 14].

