### Eligibility criteria

#### Inclusion criteria

The inclusion criteria are as follows: (1) patients who have a history of hepatitis B infection or HBsAg positive for more than 6 months, and their current HBsAg and/or HBV DNA levels are still positive; (2) patients who meet the criteria for antiviral indications in the “Asian-Pacific consensus statement on the management of CHB: a 2008 update” [27]; patients taking entecavir dispersible tablets may also be included. (This study will enroll patients who have taken entecavir previously; conversely, patients who have taken immune stimulatory drugs or other antiviral drugs within 3 months will not be enrolled.); (3) patients between 18 to 65 years old; (4) patients showing syndromes of liver stagnation and spleen deficiency and dampness in TCM. For the TCM diagnostic criteria, we refer to “National Standards for TCM Clinical Diagnosis and Treatment in the People’s Republic of China” [28] and the “Medical Consensus of diagnosis and treatment of cirrhosis with integrated TCM and Western medicine” [29], published by the Digestive System Diseases Committee, Society of Integrated Traditional Chinese and Western Medicine.

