### Allocation

#### Sequence generation and implementation

A central randomization system (CRS) is applied to ensure a completely randomized design. The randomized system mainly includes the following modules: subject screening, randomization, emergency unblinding, drug formulation, drug supply management, and other functional modules. The central randomization principle is as follows: The researcher uses the screening module to enter some basic information for the subject (such as date of birth, gender) and obtain the subject’s unique identification number (SIN). Firstly, the researcher confirms that the patient meets the inclusion criteria, logs into the CRS, inputs the general information for the subject, generates the random number, and fills in the eCRF. Secondly, drug distributors apply for the drug number from the CRS according to the random number. Finally, the drug senders verify the code on the drug package with the number in the system, and then the drugs are given to the patients.

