### Statistics

#### Outcomes

For the statistical analysis comparing the primary outcome incidence between the two groups, we will use the χ^2^ test and set *P* < 0.05 (95% confidence interval) as statistically significant. For the secondary outcomes, the measurement data are expressed as mean ± standard deviation, the count data are expressed as frequency and percentage (*f*, %), and the frequency or percentage of the efficacy evaluation index is converted into frequency and percentage (*f*, %). For comparison of the mean between the two groups, the homogeneity test is performed first. If the variances are equal, the *t* test is used. If the variances are unequal, the non-parametric *t* test is used. The measurement data of each group before and after treatment are compared using the paired *t* and/or *t* test. The comparison of grid table count data will be performed using the χ^2^ test, and the comparison of rank data will use the rank sum test. *P* < 0.05 will be used as the statistical difference. The data analysis will be performed using SPSS 19.0 statistical software.

The baseline is defined as the last observation data before the first medication, which includes demographic characteristics and clinical baseline data: age, sex, vital signs (height, weight, temperature, heart rate, blood pressure, breathing), clinical symptom scores, HBV DNA, liver stiffness (FibroScan/Fibrotouch), entecavir treatment history, and CHB-related diseases.

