#### Analysis population and missing data

We will use three methods for statistical analysis of the data:
Full analysis set (FAS). According to the intention-to-treat (ITT) principle, all randomized subjects’ data will enter the FAS. For subjects who withdraw from the study early for various reasons, the missing data will be imputed using the method of last observation carried forward (LOCF).Per protocol set (PPS). The study’s PPS will consist of the indicator data for those who enter the study and complete treatment and follow-up, whose medication compliance is 80–120%, who took no combined medication that affected the effectiveness evaluation during the study period, and who have complete evaluation index data and no major test protocol violations.Safety set (SS). The SS includes those subjects who received at least one treatment after randomization.

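### As written, the HBV DNA and HBsAg negative rates mix patients already negative at entry with new responders, which dilutes the absolute difference and blurs its meaning

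*Protocol article*

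**What the plan says.** All references are to the Protocol article.

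- **Endpoints (Secondary outcomes).** "The secondary outcomes include HBV DNA negative rate, HBsAg negative rate, HBeAg seroconversion rate". The section gives no denominator and no condition on baseline status. It does say that these indicators are observed before treatment.
- **Entry (Inclusion criteria).** It is enough that "their current HBsAg and/or HBV DNA levels are still positive", so one positive marker suffices. On prior treatment: "patients taking entecavir dispersible tablets may also be included", and "This study will enroll patients who have taken entecavir previously". No limit is set on the share or duration of earlier entecavir.
- **HBeAg (Background).** Chronic hepatitis B is defined as covering patients with and without HBeAg, and HBeAg positivity is not an entry criterion.
- **Analysis sets (Analysis population and missing data).** "all randomized subjects’ data will enter the FAS". The per-protocol set is restricted by compliance, completeness and protocol adherence, but not by baseline marker status. Early withdrawals are imputed by carrying the last observation forward.
- **Test (Statistics, Outcomes).** "The comparison of grid table count data will be performed using the χ^2^ test". No covariate is named. HBV DNA and entecavir history are listed as baseline data.
- **Additional analyses.** No subgroup or sensitivity analyses are planned.

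**The concern.** A negative rate measures response only in patients who start positive. The entry rule admits HBsAg-positive patients whose HBV DNA is already negative, for example on earlier entecavir, which is also the background drug in both arms. In principle it also admits HBsAg-negative, HBV DNA-positive patients. If everyone randomised is in the denominator, those who enter negative and stay negative are counted as successes in both arms. The reported rate then adds maintained negativity to new negativity, and a reader cannot separate them. HBeAg-negative patients, if counted, have the opposite effect: they cannot seroconvert, so they lower the rate.

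At stake is the trial's antiviral claim. The Discussion treats long-term HBV DNA suppression or HBsAg negativity as the best surrogate endpoint, so these rates will be read as evidence of added antiviral effect. Nothing else in the described analysis would reveal the mixture. Carrying observations forward may add to it: if the baseline value counts as a last observation, a patient who enters HBV DNA negative and withdraws before week 26 becomes a success with no on-treatment measurement.

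**Working it through.** **The plan's own figure.** The Sample size section gives (1.96 + 1.282)² / [2(arcsin√0.05 − arcsin√0.01)²] = 334.5 per group, stated as 334. Then 334 × 1.2 × 2 = 801.6, stated as 802, or 401 per arm. This reproduces, but it concerns cirrhosis. The article states no figure for the antiviral outcomes.

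**Inputs.** 401 per arm and two-sided α = 0.05 come from the Sample size section. The share already negative (f) and the response rates among patients at risk (positive for the marker at baseline) are not in the article. They are assumptions, shown over a range.

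**HBV DNA.** Suppose patients negative at entry stay negative in both arms, and a proportion p of those positive become negative. Then:

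- reported rate = f + (1 − f)p
- reported difference = (1 − f)(p_YQSH − p_placebo)

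The second line needs only that baseline-negative patients have the same rate in both arms. It need not be 100%.

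Power uses the pooled-variance normal approximation, with d the difference, p̄ the mean of the two rates and n per arm:

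power = Φ{[d√n − 1.96√(2p̄(1 − p̄))] / √[p₁(1 − p₁) + p₂(1 − p₂)]}

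Worked case, f = 50%, 80% v 70% at risk:

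- All randomised: 0.90 v 0.85, n = 401. (0.05 × 20.025 − 1.96 × 0.4677) / 0.4664 = 0.181, power 57.2%.
- At risk only: 0.80 v 0.70, n = 200. (0.10 × 14.142 − 1.96 × 0.6124) / 0.6083 = 0.352, power 63.8%.

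| f | Placebo | YQSH | Difference (points) | Power, all 401 per arm | At risk per arm | Power, at risk only |
|---|---|---|---|---|---|---|
| 0 | 70% | 80% | 10.0 | 90.6% | 401 | 90.6% |
| 25% | 77.5% | 85% | 7.5 | 77.8% | 301 | 81.0% |
| 50% | 85% | 90% | 5.0 | 57.2% | 200 | 63.8% |
| 75% | 92.5% | 95% | 2.5 | 30.9% | 100 | 37.1% |

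With 90% v 80% at risk, power is 92.1% v 93.2%, 76.8% v 80.2% and 46.1% v 50.8% at the same three shares.

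At f = 50% the fall from 90.6% to 63.8% (26.8 points) comes from having fewer patients at risk, which no analysis recovers. The further fall to 57.2% (6.6 points) comes from the denominator.

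**HBeAg seroconversion.** If HBeAg-negative patients are counted, the rate is (1 − f)p. With 18% v 10% assumed at risk and f = 50%, the report is 9% v 5%, power 60% against 64%. The risk ratio stays 1.8.

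**HBsAg.** With 3% v 1% assumed at risk:

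- f = 1%: difference 1.98 points in place of 2.00, risk ratio 1.99 in place of 3.0, power 38% against 52%.
- f = 5%: difference 1.90 points, risk ratio 1.32, power 18% against 51%.

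**The case against.** **The denominator is inferred.** No sentence says that these three rates use all randomised patients. The inference comes from the full analysis set and the absence of any set defined by baseline marker, and a fuller plan may define one. Seroconversion, by its meaning, already points to HBeAg-positive patients. This stands, and it limits the point to how the text reads. For the two negative rates the wording does not suggest a restriction, and the article rules out, for now, the subgroup analyses that could supply one.

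**A reader might infer that every antiviral effect is mis-stated, or that the test is biased.** The article does not support that. Randomisation keeps the comparison valid and the type I error intact. The HBeAg risk ratio is unchanged. The HBsAg difference barely moves if few enter HBsAg negative, which is likely because the Background defines the disease by persistent HBsAg. Even for HBV DNA, the ratio of patients remaining positive is preserved if baseline negatives stay negative: at f = 50%, 10/15 equals 20/30.

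**Maintained negativity matters too.** The outcomes are also measured at 26 and 52 weeks of follow-up after the treatment period, and the Discussion raises recurrence after drug withdrawal. An overall negative rate is therefore a defensible quantity. This stands, and it is why patients negative at entry should be reported and not dropped.

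**A reader might also infer that allocation must be stratified.** The article says "A central randomization system (CRS) is applied to ensure a completely randomized design". With a factor present in 50% of patients, the imbalance has SD √(0.25 × 2/401) = 3.5 points, and one above 5 points in either direction has a 16% chance. Even if that factor were the same as being HBV DNA negative, 5 points would move the rate by only 0.05 × (0.20 to 0.30) = 1.0 to 1.5 points. Analysis can deal with this. The defect does not require a change to randomisation during recruitment.

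**Conclusion.** The point holds as one of dilution and poor interpretability in secondary outcomes. Read as written, the HBV DNA and HBsAg negative rates combine maintained with new negativity, and the absolute difference shrinks in proportion to the share already negative. HBV DNA is the marker most exposed, because entecavir-treated patients are expressly admitted.

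Under the assumed rates, a 10-point HBV DNA effect is reported as 7.5, 5.0 or 2.5 points at 25%, 50% or 75% negative at entry. The power cost of the denominator itself is modest for HBV DNA, about 1 to 7 points over the two pairs of rates tried. For HBsAg loss it could be larger if even a few percent enter negative. The actual size cannot be computed, because the article gives neither the baseline-negative shares nor the response rates. The power figures also take all 401 per arm as analysed. The cirrhosis outcome and the sample size are unaffected.

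**What to change.** 1. Define the HBV DNA negative, HBsAg negative and HBeAg seroconversion rates among randomised patients positive for that marker at baseline. All three are measured before treatment, so no new data are needed.
2. Report maintained negativity by arm, separately, in patients negative for HBV DNA or HBsAg at baseline.
3. Compare arms by logistic regression adjusted for entecavir history and, for HBV DNA, baseline log HBV DNA. If HBsAg losses are few (1% v 3% of 401 would be about 4 v 12), use a penalised likelihood.

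The cost is smaller denominators, a second table and slightly more analysis. The change should be fixed before unblinding. The randomisation scheme can stay as it is.

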#### Safety outcomes

The safety outcomes include adverse events (AEs), laboratory tests (liver function, kidney function, routine blood tests, routine urine tests, etc.), electrocardiography (ECG), basic vital signs, and physical examination.

The basic vital signs are body temperature, blood pressure, respiration, and heart rate; laboratory tests include renal function tests, blood urea nitrogen (BUN), creatinine (Cr), and routine blood, stool, and urine tests. These biological indicators are monitored starting from the group allocation of the patients until the end of follow-up (Fig. 2).

**Fig. 2 Fig2:**
[figure not shown]
Standard Protocol Items: Recommendations for Interventional Trials (SPIRIT) schedule of enrollment, interventions, and assessments

#### Participant timeline

The treatment period is 52 weeks, and the follow-up assessment period will last for 52 ± 2 weeks. We include two figures to show the participant timeline more clearly. (See Figs. 1 and 2.)

#### Sample size

The aim of this study is to reduce the annual incidence of cirrhosis from 2% ~ 10% [30] to 1% in patients with CHB. Therefore, according to the sample size estimation formula for comparison of two sample rates, the incidence of target events is less than 0.2 (or 0.3) or greater than 0.8 (or 0.7), shown as follows:
$$ \mathrm{n}=\frac{{\left({u}_{\alpha }+{u}_{\beta}\right)}^2}{2{\left({\mathit{\sin}}^{\hbox{-} 1}\sqrt{p_e}{\hbox{-} \mathit{\sin}}^{\hbox{-} 1}\sqrt{p_c}\right)}^2} $$

Here *p*_*e*_ and *p*_*c*_ represent the incidence rates of the test group (YQSH group) and placebo group (control group), respectively. The positive event rate (*p*_*c*_) in the control group is 5%, while the target event rate (*p*_*e*_) in the test group is set to 1%. Since the values of p_e_ and p_c_ are small, the degree is measured in radians, α = 0.05, and β = 0.10. In this study, a two-sided test was chosen, *u*_0.05_ = 1.96, *u*_0.10_ = 1.282, *p*_*e*_ = 0.05, *p*_*c*_ = 0.01. The calculated sample size of each group is approximately 334 cases. Therefore, allowing for 20% attrition, the total number of patients required for this trial is 334*(1 + 20%)*2 = 802 cases, with 401 in each group.

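### The 20% attrition allowance multiplies by 1.2 instead of dividing by 0.8, so 401 per group covers only 16.7% loss; the cost in power is about 1.2 points

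*Protocol article*

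**What the plan says.** All the sample size inputs are in the protocol article, section Sample size. The error rates are "α = 0.05, and β = 0.10", and "a two-sided test was chosen". In words, the positive event rate "in the control group is 5" per cent and the target rate "in the test group is set to 1" per cent. An arcsine formula for two proportions is applied, with the result: "The calculated sample size of each group is approximately 334 cases". The allowance for loss follows: "allowing for 20% attrition, the total number of patients required for this trial is 334*(1 + 20%)*2 = 802 cases", split as 401 per group.

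In the list of values put into the formula, the same section gives "p*_*e*_ = 0.05, *p*_*c*_ = 0.01", although it has just defined the first symbol as the YQSH rate and the second as the placebo rate.

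Three other sections bear on the point. Statistics, Outcomes names the chi-square test for the primary outcome. Analysis population and missing data puts every randomised patient in the full analysis set (FAS), fills in early withdrawals by last observation carried forward (LOCF), and limits the per protocol set to those who complete treatment and follow-up. Primary outcome places the assessments before treatment, at 52 weeks of treatment, and at the 52 ± 2 week follow-up visit.

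**The concern.** Attrition is a fraction of the patients randomised. If a fraction d is lost, N randomised leaves N(1 − d), so keeping n requires N = n/(1 − d). The plan uses N = n(1 + d), which is always smaller. The section therefore claims cover against 20% loss that 401 per group does not give.

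At stake is whether the stated attrition cover and the 90% design power can both be relied on. A reader who sees 20% attrition in the final report would take the trial to have kept its planned 334 per group, and it would not have.

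The swapped rates are a separate slip in the same calculation: the listed inputs contradict the definitions just above them.

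**Working it through.** **Inputs (Sample size section).** Control rate 0.05, YQSH rate 0.01, u = 1.96 (two-sided 0.05) and 1.282 (β = 0.10), attrition 20%, equal groups.

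**1. Reproducing the plan's figure.** With angles in radians:
- asin√0.05 = 0.22551; asin√0.01 = 0.10017; difference Δ = 0.12535
- n = (1.96 + 1.282)² / (2Δ²) = 334.48, printed as 334
- 334 × 1.2 × 2 = 801.6, printed as 802, or 401 per group

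Both printed figures are reproduced. Because Δ is squared, exchanging the two rates leaves n unchanged.

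**2. The attrition step.**
- Needed: 334 / (1 − 0.20) = 417.5, so 418 per group and 836 in total
- Planned: 401 per group and 802 in total, which is 17 per group and 34 in total fewer (34/836, about 4%)
- Loss that 401 can absorb: 1 − 334/401 = 16.7%
- Left after 20% loss: 401 × 0.80 = 320.8, about 321 per group, 13 short of 334

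**3. Power for 5% v 1%.** By the plan's formula, power = Φ(√(2n) × Δ − 1.96). The exact column enumerates the uncorrected chi-square test.

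| Patients per group | √(2n) × Δ | Arcsine power | Exact chi-square power |
|---|---|---|---|
| 334 (target) | 3.240 | 90.0% | 89.8% |
| 321 (completers at 20% loss) | 3.176 | 88.8% | 88.6% |
| 401 (nobody lost) | 3.550 | 94.4% | 94.2% |

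Compared within one method, the attrition step costs about 1.2 points on either.

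**4. The FAS with LOCF.** The FAS denominator stays at 401 per group. Patients with cirrhosis are excluded at entry, and the first assessment of the primary outcome after baseline is at week 52. A patient lost before then therefore has only a cirrhosis-free baseline to carry forward. Assume, as the least favourable timing, that all 20% are lost before week 52 and would have had the same event rates as the rest:
- Observed rates: 0.05 × 0.8 = 0.04 and 0.01 × 0.8 = 0.008
- asin√0.04 − asin√0.008 = 0.20136 − 0.08956 = 0.11180
- √802 × 0.11180 = 3.166; Φ(3.166 − 1.96) = 88.6% (arcsine); exact chi-square 87.8%

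Later losses would dilute the rates less, because some of those patients would have a week 52 assessment.

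**The case against.** The strongest reply is that almost nothing follows from the error. Power falls by 1.2 points and the sample is about 4% short. Setting the exact 88.6% against the nominal 90% would also mix methods, since exact power at the intended 334 is itself only 89.8%. All of this stands, and it limits how much weight the point can bear.

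A second reply is that the primary comparison need not lose anyone: the FAS keeps all 401 per group, with nominal power of 94.4%. This stands in part. The figure of 321 describes a completers analysis and must be labelled so. But 94.4% holds only if the imputed values are as informative as observed ones. Under the early-loss assumption in the working, the FAS also ends at about 88-89%, so LOCF cannot be counted on to restore the cover.

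Three stronger readings are tempting and are not supported:
- A reader might infer that the trial is seriously underpowered because of the attrition step. The figures above show a marginal shortfall.
- A reader might take the swapped rates to mean that the plan expects more cirrhosis on YQSH. The same section states the 5% and 1% in words with the right groups, and the Abstract and Background repeat the 1% target for the combination. It is a labelling slip.
- A reader might fault the choice of 5% because both groups receive entecavir, or because power would be low near the bottom of the cited range. The section prints the range openly ("The aim of this study is to reduce the annual incidence of cirrhosis from 2% ~ 10% [30] to 1% in patients with CHB") and names the value it selects. Whether the cited range comes from treated or untreated patients cannot be told from the documents, and the question is separate from the attrition arithmetic.

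**Conclusion.** The point holds as a certain arithmetic error with a small consequence. The section claims cover for 20% attrition; 401 per group covers 16.7%, and the claimed cover would need 418 per group. At 20% loss the power for 5% v 1% is about 89% among completers, roughly 1.2 points below the design value.

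This rests on the plan's own rates, significance level and formula, on equal loss in the two groups, and, for completers, on loss unrelated to outcome. The FAS figure of about 88-89% rests further on the assumption that every loss comes before week 52. The swapped input line is a real contradiction within the section and has no effect on n.

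**What to change.** Keep 802 and change the wording of the Sample size section in two places.

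1. Replace the attrition sentence with one to this effect: 401 per group (802 in total) allows for 16.7% attrition; at 20% attrition about 321 completers per group remain, giving about 89% power for 5% v 1% in a completers analysis. Add that the FAS keeps 401 per group by LOCF, and that if all 20% were lost before week 52 and carried forward as free of cirrhosis (an assumption), its power would also be about 88-89%.
2. Correct the input line to p_e = 0.01 and p_c = 0.05, in agreement with the definitions in the same section.

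The cost is wording only, and a slightly less favourable stated power. If the sponsor prefers to keep the claim of 20% cover, the consistent number is 418 per group, 836 in total, which means 34 more patients.
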